## Abstract

**Background:**

Although coronavirus disease 2019 (COVID-19) is primarily a respiratory illness, myocardial injury is increasingly reported and associated with adverse outcomes. However, the pathophysiology, extent of myocardial injury and clinical significance remains unclear.

**Methods:**

COVID-HEART is a UK, multicentre, prospective, observational, longitudinal cohort study of patients with confirmed COVID-19 and elevated troponin (sex-specific > 99th centile). Baseline assessment will be whilst recovering in-hospital or recently discharged, and include cardiovascular magnetic resonance (CMR) imaging, quality of life (QoL) assessments, electrocardiogram (ECG), serum biomarkers and genetics. Assessment at 6-months includes repeat CMR, QoL assessments and 6-min walk test (6MWT). The CMR protocol includes cine imaging, T1/T2 mapping, aortic distensibility, late gadolinium enhancement (LGE), and adenosine stress myocardial perfusion imaging in selected patients. The main objectives of the study are to: (1) characterise the extent and nature of myocardial involvement in COVID-19 patients with an elevated troponin, (2) assess how cardiac involvement and clinical outcome associate with recognised risk factors for mortality (age, sex, ethnicity and comorbidities) and genetic factors, (3) evaluate if differences in myocardial recovery at 6 months are dependent on demographics, genetics and comorbidities, (4) understand the impact of recovery status at 6 months on patient-reported QoL and functional capacity.

**Discussion:**

COVID-HEART will provide detailed characterisation of cardiac involvement, and its repair and recovery in relation to comorbidity, genetics, patient-reported QoL measures and functional capacity.

*Clinical Trial registration:* ISRCTN 58667920. Registered 04 August 2020.

## Background

The coronavirus disease 2019 (COVID-19) severe acute respiratory syndrome coronavirus 2 (SARS-CoV-2) pandemic [1] was initially recognised as a primarily respiratory illness with a severe acute respiratory syndrome, but it is now known that it can affect multiple organs with a wide spectrum of disease severity [2, 3].

The direct cardiovascular impact of COVID-19 is three-fold. Firstly, underlying cardiovascular disease (CVD) can predispose patients to the infection and is associated with an increased illness severity. Secondly, COVID-19 may exacerbate underlying cardiovascular co-morbidities leading to symptom destabilisation and potentially acute admission to hospital. Thirdly, de novo cardiac complications of COVID-19 may occur [4], with SARS-CoV-2 infection being implicated in acute myocarditis, pericarditis, prothrombotic complications, left ventricular (LV) and/or right ventricular (RV) dysfunction, arrhythmia and ischaemic sequelae in the presence or absence of underlying coronary artery disease (CAD) [1, 4–6].

Multiple studies have demonstrated that myocardial injury, characterised by elevation in serum cardiac biomarkers, is common in COVID-19. The prevalence of myocardial injury, however, is variably reported, with early studies quoting a prevalence of 8–12% in hospitalised patients, whilst more recent data suggest that it is possibly much higher [4, 7]. Subsequently, a larger multicentre study of 305 patients identified an elevated troponin in more than half of the hospitalised patients [8]. A recent German cohort study reported imaging evidence of myocardial injury defined by cardiovascular magnetic resonance (CMR) in over 70%, although whether this was pre-existing or consequence was unclear with single time-point imaging [9]. The underlying mechanism of cardiac injury and troponin elevation remains unclear, but there are several potential explanations. Troponin T release is commonly seen in critically ill patients because of oxygen supply–demand mismatch and cytokine release, acute heart failure, RV strain (secondary to pneumonia, hypoxia and increased pulmonary artery pressure) and acute arrhythmia [10–12]. Furthermore, the acute-phase response to severe coronavirus infection can lead to coagulopathy and microvascular thrombosis, for example in the pulmonary and coronary circulations [13, 14]. Pre-existing coronary risk factors, such as hypertension and diabetes also predispose patients with COVID-19 to myocardial infarction in the acute setting, possibly implicating it as another potential disease mechanism [15]. On a cellular level, however, direct myocardial injury may occur due to viral angiotensin-converting enzyme-2 transmembrane receptor mediated damage, microvascular dysfunction or increased vessel wall permeability [16].

Troponin elevation in hospitalised COVID-19 patients is associated with higher morbidity and increased short-term mortality [4, 8, 17–21], particularly in those who also have underlying CVD [16]. Those with CV comorbidities (diabetes, hypertension, heart failure or CAD/peripheral artery disease) are heavily over-represented in both severe COVID-19 and mortality [22, 23].

An elevated troponin should prompt a search for causation, and particularly imaging, as structural abnormalities are likely to be found in this cohort and further predict adverse outcomes (Fig. 1) [4, 8, 17–20, 24]. In patients with an elevated troponin and non-obstructive coronary arteries, CMR can provide the diagnosis in up to 90% of cases [25], and  is the imaging modality of choice for diagnosis of acute myocarditis [26]. The diagnostic performance of the CMR-Lake Louise imaging criteria to identify acute myocarditis has been reported to have an overall diagnostic accuracy of around 83% (sensitivity 78–80% and specificity ~ 87–88%) [27, 28]. CMR can also identify persistent inflammation and the presence of fibrosis in patients recovered from COVID-19 [9, 29], which may have long-term clinical implications. Furthermore, CMR is the reference standard method for assessing LV and RV pathology, whilst regional perfusion defects consistent with obstructive CAD can be accurately identified using CMR perfusion [30].

**Fig. 1 Fig1:**
[figure not shown]
Electrocardiogram (ECG) and cardiovascular magnetic resonance (CMR) examples in troponin positive COVID-19. Potential diagnoses include: no abnormalities detected, myocarditis, infarction, dual pathology and pericardial inflammation. First example shows a normal 12-lead electrocardiogram (ECG) and a normal CMR study. Second example shows myocarditis, with anterolateral ST segment flattening. CMR shows normal function but patchy mid-wall enhancement in the anterior and inferior wall (red arrows) with T2 map showing co-localised oedema. The third example shows myocardial infarction with ECG anterolateral ST changes and thinning of left ventricular (LV) wall predominantly in the anterolateral segment on the short-axis image (red asterisk); corresponding LGE image shows an ischaemic pattern transmural scar (red arrow); T1 maps show elevated T1 values in the lateral wall. The fourth example shows a case of dual pathology due to myocarditis and infarction. The ECG shows hyperacute T-waves in the anterolateral leads and the CMR study shows a short-axis cine with increased signal intensity in the anterior/anteroseptal segment (red asterisk). The two LGE images reveal an ischaemic scar in this area extending from subendocardium as well as an area of sub-epicardial enhancement in the inferior wall consistent with myocarditis (red arrows). The last case presents pericardial inflammation. The ECG shows widespread concave ST-segment elevation. The 4-chamber cine is unremarkable, whereas the corresponding LGE images show pericardial enhancement (red arrows)

Based on the possibility that myocardial injury may be relatively common in COVID-19 patients, and has been shown to be a marker of poor prognosis, further studies are required to clarify the pathophysiology of SARS-CoV-2 related myocardial injury. In particular, the nature of injury may suggest the need for therapeutic intervention, which may be specific (e.g. antithrombotic, anti-inflammatory), or non-specific e.g. heart failure treatment. Importantly, the nature and extent of myocardial injury may also help risk stratify patients both acutely and chronically, and for this, multi-time-point imaging is required to separate out cause and effect. Finally, the underlying risk factors for myocardial involvement and the impact on long-term clinical outcomes need to be investigated.

## Methods

### Objectives

The primary objectives of COVID-HEART are, for a hospitalised-recovering patient population (or those recently discharged), to: (1) characterise the nature and extent of myocardial involvement in COVID-19 patients with an elevated troponin; (2) assess how cardiac involvement and clinical outcome associate with recognised risk factors for mortality in COVID-19 (age, sex, ethnicity and comorbidities) and with genetic factors; (3) evaluate if differences in myocardial recovery at 6-months are dependent on demographics, genetics and CVD comorbidities (diabetes, hypertension, heart failure and CAD/peripheral vascular disease); (4) understand the impact of recovery status at 6-months on patient-reported quality of life (QoL) and functional capacity.

The secondary objectives include: (a) to examine whether there are characteristic electrocardiogram (ECG) findings specific for SARS-CoV-2 myocarditis that are distinct from acute myocardial infarction which could minimise the requirement for invasive cardiac catheterisation and, (b) to establish the nature and prevalence of myocardial ischaemia and microvascular dysfunction (coronary vascular sub-study).

### Study design

A longitudinal, multicentre, observational cohort study of UK patients presenting with COVID-19 and elevated serum troponin, who are either recovering in hospital or were recently discharged.

### Ethics and registration

Ethical approval for the COVID-HEART study has been granted by the UK National Research Ethics Service (20/NW/0292). COVID-HEART is registered on the 'International Standard Randomised Controlled Trial’ registry (ISRCTN 5866,920) https://doi.org/10.1186/ISRCTN58667920.

### Study population

Inclusion criteria include—hospitalised-recovering patient population (age ≥ 18 years), or those recently discharged from hospital, with a diagnosis of COVID-19 based upon either a pathology or radiology diagnosis, with cardiac biomarkers (troponin I or T) increased above the sex-specific upper reference limit of the local laboratory range. Exclusion criteria include being unable or unwilling to consent, contraindication to CMR, pregnancy or breast-feeding.

Contemporary patient cohorts acting as control data will be acquired for comparative CMR analysis. These will be derived from ethically approved local research studies from the recruiting centres for COVID-HEART using the same CMR scanners (vendor and field strength). As the patients in COVID-HEART are COVID( +) and Troponin( +), control populations will include:A population matched for age and CVD risk factors, who have been hospitalised and are COVID( +) and Troponin(−) [e.g. Capturing MultiORgan Effects of COVID-19 (C-MORE) cohort, Oxford, UK; NCT04510025].A population matched for age and CVD risk factors, who have tested COVID(−) and Troponin(−).

### Setting

Recruitment will take place in 25 participating secondary or tertiary care hospitals across the UK, all of whom have access to well-established local CMR services.

### Recruitment process and data collection

Screening will be performed at an individual hospital level, with participating hospitals cross-referencing all admissions with a positive COVID-19 status (pathology/radiology diagnosis), with serum troponin results. This study will integrate two key aspects. Work package-1 will establish a national image repository for patients with COVID-19 who have CMR for clinical reasons. Work package-2 (objectives as outlined above) will use CMR to characterise the nature and extent of myocardial injury in a hospitalised but recovering patient population, who are serum biomarker (troponin) positive for myocardial damage.

The source data will include hospital records, National Health Service (NHS) health and social care records, clinical and office charts, laboratory and pharmacy records as well as digital images from radiology (chest X-ray/computed tomography/CMR) and cardiology (echocardiography/angiography/CMR). Patients in work package-1 who have a clinically indicated CMR and are troponin positive will be invited to join work package-2 for a follow-up CMR scan and assessment at 6 months. Clinical follow up for vital status and cardiovascular events at 12 months (and up to 5-years) will be performed by recruitment sites via local hospital electronic patient records, primary care records and by national data-linkage for other NHS databases.

Co-enrolment of patients in existing registries will be encouraged (e.g. ISARIC-4c and CAPACITY: Cardiac complicAtions in Patients with SARS Corona vIrus 2 regisTrY; NCT04325412). Also, as this is a longitudinal, observational study, co-enrollment with other UK COVID-19 studies/trials will be permitted.

### Consent procedures

All recruited patients will provide written informed consent as per the international ethical and scientific quality standard of Good Clinical Practice (GCP). Patient information sheets for COVID-HEART will be provided in English, and also in up to 10 other languages commonly spoken in the UK, including: French, Portuguese, Polish, Urdu, Bengali, Punjabi, Gujarati, Hindi, Somali and Arabic.

When eligibility criteria are confirmed, medical staff or appropriately trained support staff will seek consent from patients after allowing as much time as necessary to consider the study, or at least 24 h, whilst the patient is either an in- or out-patient. Consent for participation in the coronary vascular sub-study (ethics reference: 19/EM/0295) will be sought at the time of consent for work package-2.

All participants will have the right to withdraw from the study at any point. Moreover, the investigator may discontinue a participant from the study at any time if it is considered necessary for any reason including ineligibility, significant protocol deviation or loss to follow-up. The reason for withdrawal will be recorded. If consent is withdrawn before data are used in any research analyses, then data relating to that participant could be removed, if the participant explicitly requests that their data are not used. In general, if consent is withdrawn, or if the patient were to become incapacitated, any data collected up to that point will remain on file and will be included in the final study analysis.

### Research investigations

All recruited patients will be offered CMR imaging, digital 12-lead ECG, validated quality of life questionnaires, 6 min walk test (6MWT), and additional blood sampling for genetic analysis/immunological responses/T-cell function and cardiovascular biomarkers, if not already acquired. See study flow diagram (Fig. 2) and below for detailed description of research investigations.

**Fig. 2 Fig2:**
[figure not shown]
Study flow diagram. COVID-19 patients, who have an elevated troponin, will be invited to participate in the study. Patients who are recruited undergo multimodality assessment at index visit: either during their hospital admission or within 28 days of discharge. Assessment includes a 12-lead ECG, CMR study, genetic and immunological blood tests, and Quality of Life questionnaires. Patients are subsequently invited for a second visit at 6 months. At this point they undergo a repeat CMR scan, quality of life assessments and 6-min walk test. Further follow up at 12 months will be conducted via examination of routine clinical data, available through general practitioners, electronic hospital records, NICOR and NHS Digital, and in collaboration with other nationally recognised COVID-19 studies

1)* CMR* Scans will ideally be performed pre-discharge or within 28 days of discharge, and then repeated at 6 months (± 4 weeks) from the date of admission and on the same scanner wherever possible. Scans will be performed on either a 1.5 T or a 3 T CMR system using multi-channel phased-array chest coils of any vendor, depending upon local availability. ECG gating will be employed for all cardiac gated sequences to ensure appropriate triggering. The main CMR protocol is in keeping with Society for Cardiovascular Magnetic Resonance (SCMR) recommended CMR protocols for scanning patients with active or convalescent phase COVID-19 [6], and it will take approximately 50 min to acquire, with an optional shortened and extended protocol dependent of patient preference and ability. An estimated glomerular filtration rate (eGFR) and haematocrit will be measured prior to each CMR scan. For patients with significant renal failure (eGFR < 30 ml/min/1.73 m^2^), late gadolinium enhancement (LGE) and post-contrast T1-mapping can be omitted and a contrast-free CMR scan performed.

The main CMR study protocol includes the following components and typical parameters, which may vary by vendor and field strength, but remain comparable overall (Fig. 3):A.Localiser sequences and breath-hold transverse Half-Fourier Acquisition Single-shot Turbo spin Echo (HASTE) imaging stacks covering lung and abdomen to 1–2 cm below the kidneys. Typical sequence parameters: TE 1.33 ms, TR 700 ms, slice thickness 8 mm, FOV = 400 mm, FOV phase 100%, flip angle 10°.B.Cine images acquired with breath-hold balanced steady-state free precession (bSSFP) sequence. Long-axis views of the LV: 4-chamber, 2-chamber, and 3-chamber views. Sequence parameters: TE 1.05 ms, TR 40.29 ms, slice thickness 8 mm, 25% distance factor, FOV = 500 mm, FOV phase 75%, flip angle 50°.C.Native (pre-contrast) T1-mapping: acquired using a single breath-hold shortened modified Look-Locker inversion (ShMOLLI) 5(1)1(1)1 technique [31], where available. Shimming will be performed to avoid artefacts. Native T1-mapping will be acquired in 3 short-axis cuts of the LV (basal, mid-ventricular, apical) to match the locations of segments 1–16 of the American Heart Association 17-segment model [32]. The apical segment 17 is omitted. Each acquisition will be verified against an R^2^ map (according to vendor availability). Typical pulse sequence parameters: TE 1.07 ms, TR 379 ms, slice thickness 8 mm, FOV = 360 mm (can be adjusted according to size), FOV phase 75%, flip angle 35°, distance factor 25%, generalised auto-calibrating partially parallel acquisition (GRAPPA) 2 with 24 reference lines.D.Native (pre-contrast) T2-mapping: matching in slice location to the T1 maps, will be acquired using either a T2-prepped b-SSFP sequence with a minimum of 3 source images (e.g. MyoMaps T2-mapping for Siemens scanners), or a black-blood prepared, navigator-gated, free-breathing hybrid gradient (echo planar imaging, EPI) and spin-echo multi-echo sequence (GRASE). Typical sequence parameters: TE 1.3 ms, TR 222.43 ms, slice thickness 8 mm, FOV = 360 mm, FOV phase 80%, flip angle 20°.E.Rest myocardial perfusion imaging: obtained using pixel-wise perfusion mapping (or locally available pulse sequence) following administration of 0.05 mmol/kg of gadolinium based contrast agent (GBCA) at 4 ml/s with 20 ml flush at 4 ml/s via a power injector. Immediately after rest perfusion image acquisition, 0.1 mmol/kg top-up (giving a total dose of 0.15 mmol/kg) of GBCA will be given. Accepted GBCA agents include: gadobutrol and gadoteric acid. Sequence parameters: TE 1.04 ms, TR 143.04 ms, slice thickness 8 mm, FOV = 380 mm, FOV 75%, flip angle 50°.F.Ventricular short-axis stack. Sequence parameters will match the cine image acquisition in long-axis.G.Aortic distensibility imaging: planned using bSSFP cine sequence of the thoracic aorta in sagittal oblique view and then acquired transverse to the ascending/descending thoracic aorta (at pulmonary artery bifurcation level). Blood pressure will be recorded whilst in the scanner to allow calculation of aortic distensibility. Sequence parameters: TE 1.25 ms, TR 43.35 ms, slice thickness 6 mm, FOV = 380 mm, FOV phase 100%, flip angle 55°, 50 phases.H.LGE images will be acquired ~ 5–15 min after intravenous injection of 0.1–0.15 mmol/kg of GBCA with a free-breathing phase-sensitive motion correction bSSFP or breath-hold, segmented inversion-recovery sequence. Contiguous stack of LV short-axis images and single long-axis slices in 2-chamber, 4-chamber and 3-chamber at the same slice locations as obtained for cine imaging will be acquired. A Look-Locker sequence will be used to determine the appropriate inversion time (TI) [33]. Example parameters are: TI will be adjusted as per Look-Locker sequence, TE 1.14 ms, TR 411.48 ms, matrix 128 × 256, 8 mm slice thickness with 2 mm inter-slice gap, FOV = 400 mm, FOV phase 75%, flip angle 47°.I.Post-contrast T1 measurements will be acquired at the exact same locations as the native T1-maps and performed at least 10 min after injection of GBCA, using the same pulse sequence and parameters as the native T1-maps.J.A subset of patients eligible for coronary vascular assessment will undergo an extended protocol at baseline to include stress-perfusion imaging. Adenosine stress perfusion imaging will be acquired after post-contrast T1 mapping using an adenosine dose of 140–210 mcg/kg/min for 3–5 min, whilst monitoring symptoms, heart rate and blood pressure to assess an adequate response. Subsequently, GBCA will be given at a dose of 0.05 mmol/kg at 4 ml/s followed by a 20 ml flush at 4 ml/s, giving a total dose of 0.2 mmol/kg. Stress perfusion imaging will be acquired in the same slice locations as the rest perfusion images. Sequence parameters will match the resting scan.

2)* Digital 12-lead ECG.* A 12-lead ECG will be performed either as part of routine clinical assessment or as an additional research test during the index admission and again at 6 months follow up. In selected centres (which will be provided with an identical study-specific digital ECG machine), a full 12-lead digital ECG from COVID-19 patients will be recorded daily, if possible dependent on clinical status, for up to 7 days, whilst an in-patient. Digital ECGs in patients with CMR-proven myocarditis will be compared to a reference dataset of acute ST-elevation myocardial infarction patients already available from the NIHR-Efficacy and Mechanism Evaluation Programme funded T-TIME randomised controlled trial [34].

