2)* ECG data:* The standard and digital 12-lead ECGs will be electronically transferred via the study portal into the image repository at the coordinating centre in Glasgow, Scotland. Digital ECGs will be analysed in the University of Glasgow ECG core lab utilising the previously validated Glasgow ECG analysis software [45]. A full set of measurements plus interpretation will be extracted for analysis of ECG changes and statistical processing, with the aim of determining sensitive and specific criteria for diagnosing myocarditis from the ECG, and prognostic ECG findings in this population [46]. ECGs available in printed form will also be electronically transmitted in pdf format to the ECG Core Lab for standardised review based on the same criteria as used in the Glasgow program. Manually classified changes will also be subject to statistical analysis.

3)* Laboratory data:* All blood samples will be transferred to the central coordinating centre in Leicester, England and analysed in the University of Leicester Cardiovascular Research Centre and the BHF Glasgow Cardiovascular Research Centre, University of Glasgow. Analysis will entail novel cardiovascular biomarkers (e.g. vascular cell adhesion molecule, interleukin-6) and markers of genetic susceptibility to COVID-19. The genetic analysis will be used to explore links specifically in the black and minority ethnic populations and linked in with existing cohorts for genotyping (The Genetics and Vascular Health Check study, The Biomedical Research Informatics Centre for Cardiovascular Science and UK Biobank).

4)* 6MWT:* As per the American Thoracic Society guidelines, the distance walked (measured in meters) in 6 min will be recorded by the investigator supervising the test. Symptoms of perceived breathlessness will be recorded on the Borg scale and if the test was stopped early, the reason will be recorded.

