### Statistical analysis

Statistical analyses will be conducted after production of a signed statistical analysis plan and once baseline and follow-up data collection has been completed. Broadly, the statistical methods for each study objective will be as follows:to characterise the nature and extent of myocardial involvement in COVID-19 patients with an elevated troponin, analyses will be descriptive, and will involve estimation of prevalence with 95% confidence intervals (CIs);to assess how cardiac involvement and clinical outcomes associate with recognised risk factors for mortality in COVID-19 (age, sex, ethnicity and comorbidities) and with genetic factors, we shall present tabular and graphical descriptive summaries within subgroups, and use logistic regression to test for associations and provide estimates with 95% CIs;to evaluate if differences in myocardial recovery at 6 months are associated with demographics, genetics and CV comorbidities (diabetes, hypertension, heart failure and CAD/peripheral vascular disease), descriptive summaries, and linear and logistic regression methods will be applied;to understand the association between recovery status at 6 months and patient-reported QoL and functional capacity, descriptive methods, and linear regression will be used.

To assess whether there are characteristic ECG findings specific for SARS-CoV-2 myocarditis, measures of diagnostic performance will be calculated, and ROC analyses will be used.

In the coronary vascular sub-study, descriptive methods will be used to establish the nature and prevalence of myocardial ischaemia and microvascular dysfunction, and linear regression methods, including mixed effects methods for modelling myocardial blood flow within segments 1–16 of the American Heart Association 17-segment model, will be used to assess risk factors.

Throughout these analyses, levels of missing data will be reported, and regression models will be fitted using multiple imputation of missing predictor variables. Where appropriate, data from other cohorts will be used as control populations.

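### The only named comparator for the myocarditis ECG criteria is an external set of ST-elevation infarctions, so specificity and ROC area against it are likely inflated and do not carry over to troponin-positive COVID-19

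*Protocol article*

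**What the plan says.** Secondary objective (a), under Objectives, is to look for "characteristic electrocardiogram (ECG) findings specific for SARS-CoV-2 myocarditis that are distinct from acute myocardial infarction which could minimise the requirement for invasive cardiac catheterisation".

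Under Research investigations, item 2 (Digital 12-lead ECG), the protocol article states: "Digital ECGs in patients with CMR-proven myocarditis will be compared to a reference dataset of acute ST-elevation myocardial infarction patients". That dataset is described as "already available from the NIHR-Efficacy and Mechanism Evaluation Programme funded T-TIME randomised controlled trial".

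Under Analysis plan, item 2 (ECG data), the core-lab measurements are to be analysed "with the aim of determining sensitive and specific criteria for diagnosing myocarditis from the ECG, and prognostic ECG findings in this population". The Discussion repeats the aim of recognising myocarditis from the ECG without invasive tests.

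Under Statistical analysis, the method is: "To assess whether there are characteristic ECG findings specific for SARS-CoV-2 myocarditis, measures of diagnostic performance will be calculated, and ROC analyses will be used". That sentence does not define the non-myocarditis group. The same section says that other cohorts will serve as controls where appropriate. The two control populations under Study population are both troponin-negative and are meant for CMR comparison.

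**The concern.** Cases and comparators enter this analysis by different gates. The myocarditis cases come from the cohort, which is recruited on COVID-19 and raised troponin, and CMR classifies them. The comparators come from another trial and are, by their label, patients with ST-elevation. The ECG is the test being evaluated, so the comparators were chosen on part of the test result. A criterion that draws on the absence or form of ST-elevation will separate the two groups partly because of how they were assembled.

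The stated aims are also wider than this comparison. The objective speaks of acute myocardial infarction in general, and the Analysis plan and Discussion speak of diagnosing myocarditis. In the study's own population, the question is which troponin-positive COVID-19 patients have myocarditis and which have something else.

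At stake is how the result will be read. Because the stated purpose is to reduce catheterisation, a specificity obtained only against ST-elevation infarction could be taken as evidence that the ECG tells myocarditis from infarction in patients who were never represented among the comparators.

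**Working it through.** **No figure to reproduce.** The protocol article gives no accuracy target or sample size for the ECG analysis. Its sample size serves a different purpose, a prevalence estimate: 1.96² × 0.12 × 0.88 / 0.035² is about 331, rounded up to 332 (333 stated), and 333 / 0.90 = 370. The 12% refers to myocardial involvement, not myocarditis, so it does not give the number of myocarditis cases. The check is therefore mainly a comparison of sections.

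**Step 1: who could be a non-case in the target population.** The Fig. 1 legend lists a normal study, infarction, dual pathology and pericardial inflammation beside myocarditis. Its infarction example is described with ST changes and its dual-pathology example with hyperacute T-waves. Only the pericardial example is described with ST-elevation. The Background adds supply-demand mismatch, acute heart failure, right ventricular strain and arrhythmia as sources of raised troponin.

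**Step 2: who is named as the ECG comparator.** Only patients with acute ST-elevation infarction from an external trial. No section names a group from Step 1 as the non-myocarditis group for the ECG analysis.

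**Step 3: which accuracy measures depend on the comparator.**
- Sensitivity = share of CMR-proven myocarditis cases that meet the criterion. It uses cohort cases only. For a fixed criterion, the choice of comparator does not enter.
- Specificity = share of non-cases that do not meet the criterion. It depends wholly on who the non-cases are.
- ROC area, and any cut-off chosen from the ROC curve, depend on both groups. A cut-off tuned on the external set carries the problem into sensitivity as well.

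**Step 4: illustration of the mechanism.** The document gives no ECG rates, so every input here is an assumption. Take the simplest rule exposed to the problem: call myocarditis when ST-elevation is absent. The plan does not propose this rule; it marks the extreme of the effect.
- Assumed share of myocarditis without ST-elevation (sensitivity): 60–90%.
- Assumed share with ST-elevation in the external set: 95–100%.
- Assumed share with ST-elevation among troponin-positive COVID-19 patients without myocarditis: 5–30%.

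For this rule, specificity equals the share of non-cases with ST-elevation, and ROC area = (sensitivity + specificity) / 2.

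| Non-case group | Sensitivity | Specificity | ROC area, low end | ROC area, high end |
|---|---|---|---|---|
| External ST-elevation infarction | 60–90% | 95–100% | (0.60 + 0.95)/2 = 0.775 | (0.90 + 1.00)/2 = 0.95 |
| Cohort, no myocarditis | 60–90% | 5–30% | (0.60 + 0.05)/2 = 0.325 | (0.90 + 0.30)/2 = 0.60 |

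The same rule and the same cases give very different specificity and ROC area once the non-cases change. A criterion that relies less on ST-elevation would be affected less.

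**The case against.** The best defence has three parts.

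First, the article says only that the two groups will be compared. It does not say that the external set is the denominator for specificity or the sole non-case group. Standard, digital and printed ECGs are all sent for analysis, with no restriction to myocarditis cases, and the methods are described broadly ahead of a signed analysis plan. This stands as a limit on the point: an in-cohort comparison is open, and the unseen plan may specify it. It does not remove the point, because the article does fix one comparator, and that comparator is narrower than the aims stated beside it.

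Second, the comparison answers part of objective (a). Separating myocarditis from ST-elevation infarction matters where catheterisation is in question. This also stands: the comparator is too narrow, not irrelevant.

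Third, this is a secondary objective and ECG indices are listed as exploratory outcomes. No primary objective or sample-size figure is touched. That limits the severity.

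A reader might infer more than the document supports:
- That sensitivity is circular too. It is not for a fixed criterion, because it is measured in the cohort's own cases with CMR as reference.
- That the external ECGs were recorded at a different phase of illness. The article does not give their recording time.
- That overfitting of a many-variable ECG model adds to the problem. The article plans no such model, and that risk would apply equally to an in-cohort analysis.

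**Conclusion.** The point holds in a limited form. Specificity and ROC area estimated against the external ST-elevation set, and cut-offs tuned on it, are likely inflated by selection on the ECG and cannot be carried over to troponin-positive COVID-19 patients. Sensitivity of a fixed criterion is not affected.

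The size cannot be computed from the document. The figures above rest on assumed rates and an extreme rule, and they show the mechanism rather than an expected result. The conclusion needs two premises, both in the text: the comparators are defined as ST-elevation infarctions, and the cohort's alternatives to myocarditis are broader than that. It would lose force if the analysis plan already names an in-cohort non-myocarditis group for the main accuracy analysis. Severity: moderate.

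**What to change.** In Research investigations item 2 and in Statistical analysis, state that the main accuracy analysis for secondary objective (a) is internal to COVID-HEART:

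- CMR-proven myocarditis versus all other troponin-positive participants who have an ECG and a CMR classification.
- Separately, CMR-proven myocarditis versus participants with a CMR infarct pattern.
- Index-admission ECGs of similar timing in both groups, where available.

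Keep the ST-elevation infarction dataset for a separate, limited analysis labelled as myocarditis versus ST-elevation infarction. Do not report its specificity or ROC area as accuracy in the target population.

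The change needs no new patients or tests. The study already plans ECG and CMR for participants, and printed ECGs are reviewed centrally on the same criteria as digital ones. There are costs. There will be fewer infarct comparators. Some participants will drop out of the analysis, because investigations are offered rather than guaranteed, daily digital recording is confined to selected centres, and LGE may be omitted when eGFR is below 30 ml/min/1.73 m². Matching on timing may lose more. Intervals will be wider and the estimates probably less favourable.
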